#### Secondary outcomes

Two secondary outcomes for this trial include the following: the changes in plaque and gingival score based on Leo and silence plaque and gingival index [30] and the change in the frequency of tooth brushing per day and the perceived oral health on child’s daily life (as reported by the parents).

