### Between groups comparisons

Stata version 17 will be employed for data analysis. In a comparison of demographic (sex, gender), socioeconomic (family income, parental education), behavioral characteristics (tooth brushing frequency, usage of fluoride toothpaste, dental attendance pattern, impact of oral health on daily living, sugar intake), and caries, plaque and gingival level in both primary and permanent teeth, the difference between both intervention groups will be carried out using chi-square test for categorical variables and a *t*-test for continuous variables.

We will be reporting absolute and relative measure effect, that is, absolute and relative difference in mean for continuous outcomes (changes in the number of untreated caries) and risk difference and relative risk for categorical outcomes (changes in brushing frequency, changes in plaque and gingival conditions, changes in impact of oral health on daily living). For the primary outcome (changes in the number of untreated dental caries), negative binomial regression will be used to estimate relative difference (incidence rate ratio) and predictive margin to estimate absolute difference between intervention groups. The applied analytical technique will allow accounting for stratification of the sample and clustering of children within schools and any baseline socioeconomic difference between intervention groups. For the secondary outcome, multinomial regression will be used to estimate relative risk for the changes in frequency of daily tooth brushing and changes in the perceived oral health on child’s daily life. Predictive margins will also be used to estimate absolute difference in each secondary outcome. Intention-to-treat analysis will be used to handle missing values in all outcomes.

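### Multinomial regression is named as the source of relative risks for brushing frequency and daily-life impact, but its coefficients are ratios against a reference category and can differ from the relative risk in either direction

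*Protocol article*

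**What the plan says.** All of the relevant text except the outcome definition is in the protocol article, Between groups comparisons.

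- For categorical outcomes the article promises "risk difference and relative risk for categorical outcomes", and it lists these outcomes as "changes in brushing frequency, changes in plaque and gingival conditions, changes in impact of oral health on daily living".
- On the model, it states that "multinomial regression will be used to estimate relative risk for the changes in frequency of daily tooth brushing", and the same sentence extends this to the change in perceived oral health impact on the child's daily life.
- The next sentence reads: "Predictive margins will also be used to estimate absolute difference in each secondary outcome".
- On software: "Stata version 17 will be employed for data analysis".

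Secondary outcomes defines the two affected measures as "the change in the frequency of tooth brushing per day and the perceived oral health on child’s daily life", reported by the parents.

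The article does not give the number of change categories, the reference category or any expected category shares.

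**The concern.** The article pairs a measure with a model whose coefficients do not deliver it. It commits to a relative risk, then names multinomial regression as the means of estimating it and gives predictive margins a different job, the absolute difference. The primary-outcome text has the same structure: the negative binomial model supplies the relative measure (the incidence rate ratio) and the predictive margin supplies the absolute one. Read in parallel, the relative risk for the two secondary outcomes is the exponentiated multinomial coefficient.

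That coefficient compares arms on the ratio of one category to the reference category. It does not compare arms on the probability of the category. A reader shown it as a relative risk would take it as the ratio of the proportions improving in each arm, and could be misled about its size or even its direction. It could also contradict the risk difference printed beside it. Brushing frequency bears on the mechanism described under Primary outcome, and daily-life impact carries the quality-of-life objective, so both relative effects will be read.

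**Working it through.** **Inputs.** The model, the measure and the role of the margins come from Between groups comparisons. The article states no figure for these outcomes, so there is none to reproduce. The category structure and shares below are assumptions for illustration: three categories (worse / same / better) with 'same' as reference.

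**Formula.** Let pT_j and pC_j be the probabilities of category j in the intervention and control arms, and let ref be the reference category. In a two-arm multinomial logit,

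exp(b_j) = (pT_j / pT_ref) / (pC_j / pC_ref) = (pT_j / pC_j) / (pT_ref / pC_ref) = RR_j / RR_ref.

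So exp(b_j) = RR_j only if RR_ref = 1, that is, if the reference share is equal in the two arms. With covariates in the model, the identity holds at each fixed covariate pattern.

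**Direction.** With two categories, RR_j and RR_ref lie on opposite sides of 1, so the ratio is always further from 1 than RR_j. With three or more categories this no longer follows. For a category with RR_j above 1:

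- if the reference share falls in the intervention arm, the coefficient exceeds RR_j;
- if it rises, the coefficient is below RR_j;
- if it rises proportionally more than category j does, the coefficient falls below 1.

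**Numbers for 'better'.**

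| Case | Control (worse/same/better) | Intervention | RR, better | RR, same | Coefficient = RR better / RR same |
|---|---|---|---|---|---|
| A | .10/.60/.30 | .08/.50/.42 | .42/.30 = 1.40 | .50/.60 = 0.833 | 1.68 (further from 1) |
| B | .10/.60/.30 | .05/.60/.35 | .35/.30 = 1.17 | .60/.60 = 1.00 | 1.17 (equal) |
| C | .30/.40/.30 | .10/.50/.40 | .40/.30 = 1.33 | .50/.40 = 1.25 | 1.07 (nearer 1) |
| D | .30/.40/.30 | .15/.52/.33 | .33/.30 = 1.10 | .52/.40 = 1.30 | 0.85 (opposite side of 1) |

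One data set can err in both directions. In case A the relative risk for 'worse' is .08/.10 = 0.80, while the coefficient is 0.80/0.833 = 0.96, which is nearer to 1.

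Case D shows the clash with the absolute measure. The risk difference for 'better' is .33 − .30 = +0.03, yet the figure labelled relative risk would be 0.85.

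**Check by fitting.** A multinomial logit fitted to data with the case A shares returned exponentiated coefficients of 0.96 (worse) and 1.68 (better). The predicted probabilities from the same fit were .30 and .42 for 'better', giving a relative risk of 1.40 and a risk difference of +0.12. The quantity the article promises is therefore available from the model it names, through the predicted probabilities.

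**The case against.** The best defence is that the article never says in terms that coefficients will be reported as relative risks. A multinomial model can yield relative risks through its predicted probabilities, and predictive margins are already planned for each secondary outcome. The phrase may also be shorthand for the relative-risk ratio, which is Stata's label for this model's output. The article condenses a fuller plan, and the reference category and post-estimation steps are commonly left to the analysis plan.

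Part of this stands. The coefficient reading is an inference, and the absence of a reference category or of post-estimation detail is not itself an error. What does not stand is that the text is sound as written: it gives the margins the absolute difference only and ties the relative risk to the regression, parallel to the primary outcome. If shorthand was meant, the measure still differs from the relative risk promised for categorical outcomes in the same section.

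A reader might infer something stronger: that the effects on brushing and daily-life impact would be overstated, as an odds ratio overstates a relative risk for a common outcome. The document does not support that. The rule belongs to two-category outcomes. With three or more, overstatement of a benefit requires the reference share to fall in the intervention arm, and no shares are given. A shift from unchanged to improved brushing would produce that fall, but an intervention that mainly prevents worsening could raise the unchanged share, as in cases C and D.

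**Conclusion.** The point holds as a mismatch between the stated measure and the named model. Read as written, the reported relative risk would be RR_j / RR_ref, which is the wrong quantity unless the reference share is the same in both arms. The error can go either way; the worked values are 1.68 against 1.40, 1.07 against 1.33 and 0.85 against 1.10. These rest on assumed three-category splits with 'same' as reference. They show what is possible and are not a range for this trial.

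Severity is low. Two parent-reported secondary outcomes are affected, and for those only the relative measure. The negative binomial analysis of the primary outcome, the sample size and the margin-based risk differences do not depend on this.

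**What to change.** Amend the secondary-outcome sentences in Between groups comparisons so that both effect measures come from one source. For each change category, the risk difference and the relative risk would be the difference and the ratio of the arm-specific predicted probabilities, taken from the predictive margins of the same multinomial model with clustering by school allowed for. Give each a delta-method or bootstrap interval that respects the clustering. If the exponentiated coefficients are also shown, call them relative-risk ratios and name the reference category.

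The cost is a sentence or two of wording. The model and the margins are already planned; the only added analysis is a ratio of margins and its interval. No change to data collection or sample size is needed.

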## Discussion

Despite the availability of free dental services in Saudi Arabia, dental caries is still a common disease among children. Many studies have focused on the implementation of school-based programs to promote and tackle the burden of untreated dental caries [34]. This study will take a step further and explore the effectiveness of virtual supervised tooth brushing on untreated dental caries especially since Saudi Arabia has proven to have an effective IT infrastructure for virtual schooling.

Three different outcome measures are used to evaluate the effectiveness of virtual supervised tooth brushing on caries experience. The study’s primary outcome is the change in caries experience—the number of decay (untreated dental caries) missing and filled teeth—in both primary and permanent teeth over 36 months (baseline, + 3 months,+ 6 months + 12 months,+ 24 months, + 36 months from baseline) using the WHO criteria [29]. The secondary outcome will be obtained through both clinical outcomes (plaque and gingival scores) and the self-reported questionnaire to assess the change in the frequency of brushing per day and the impact of oral health on the child’s daily life (QoL) [29]. The selected study design will collect data on participants’ socioeconomic and behavioral factors which will help accounting for baseline differences between the two trial groups.

The findings of this study will provide important information on the impact of virtual supervision on dental caries. A positive impact will be an opportunity for targeting a large portion of the population with a high level of disease as a quarter of the Saudi population is younger than 15 years [1]. A positive finding will also support the continuation of virtual supervised tooth brushing in many schools in other parts of the country. Finally, future research should also investigate the factors that could affect the effectiveness of programs. A national study could provide more details about the effectiveness of the program in many different parts of the country.

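### Brushing frequency and oral-health impact are analysed as categorical changes with no named adjustment for the child's own baseline answer, which costs precision and makes two secondary results harder to interpret

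*Protocol article*

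**What the plan says.** The Secondary outcomes section defines both measures as change: "the change in the frequency of tooth brushing per day and the perceived oral health on child’s daily life (as reported by the parents". The Objectives do the same and frame the quality-of-life objective as an improvement.

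Between groups comparisons sets the effect measures: "risk difference and relative risk for categorical outcomes (changes in brushing frequency, changes in plaque and gingival conditions, changes in impact of oral health". It then names the model: "multinomial regression will be used to estimate relative risk for the changes in frequency of daily tooth brushing". Further along, that model is extended to the quality-of-life measure: "changes in the perceived oral health on child’s daily life. Predictive margins will also be used to estimate absolute difference in each secondary outcome".

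On baseline, the sentence after the primary-outcome model speaks of "accounting for stratification of the sample and clustering of children within schools and any baseline socioeconomic difference between intervention groups". The Discussion adds that the design will gather information on "participants’ socioeconomic and behavioral factors which will help accounting for baseline differences between the two trial groups". Neither place names the child's own baseline brushing frequency or baseline impact as a covariate for these two outcomes. Table 1 shows that both answers are collected at baseline and at later visits. No section says what the change categories are.

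**The concern.** Brushing times per day and reported impact on daily life come from a questionnaire and are most plausibly short ordered scales with a top and a bottom. The direction of change on such a scale discards the level:

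- A child who brushes twice daily at both visits and a child who never brushes at either visit are both *same*.
- A child who moves from never to once a day is *increased*, and so ranks above the child who brushed twice daily throughout.
- A child at the top at baseline cannot be *increased*. If the programme stops that child slipping back, the benefit shows only as fewer children in *decreased*.

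The risk of improvement then reflects where children started as well as what the programme did. With 20 schools, some baseline difference between arms is to be expected. Brushing frequency is also the behaviour through which the Primary outcome section expects caries to fall, so an imprecise or baseline-driven brushing result would weaken interpretation of the caries result.

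**Working it through.** The plan gives no rate, effect size or power for these two outcomes, so there is no figure of its own to reproduce. Everything below except the sample-size inputs is an assumption.

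**Inputs from the protocol article.** There are 596 children per arm, 20% dropout, 20 schools allocated 1:1 and an ICC of 0.02. Analysed per arm: 596 × 0.8 = 476.8; per school: 476.8 / 10 = 47.7, taken as 48. The ICC is the one used for sizing the trial on caries; applying it to brushing is an assumption.

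**1. Where the effect goes (two-level illustration).** Let *b* be the share of good brushers at baseline. Assume poor brushers become good in 20% (control) and 35% (intervention), and good brushers stay good in 85% and 90%.

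- Risk difference for *improved* = (1 − b)(0.35 − 0.20).
- Difference in follow-up level = (1 − b)(0.35 − 0.20) + b(0.90 − 0.85).
- Good-throughout share of control *same* = 0.85b / [0.85b + 0.80(1 − b)].

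| b | Can ever improve | RD improved | RD follow-up level | Good-throughout share of control *same* |
|---|---|---|---|---|
| 0.20 | 80% | 0.120 | 0.130 | 21% |
| 0.50 | 50% | 0.075 | 0.100 | 52% |
| 0.80 | 20% | 0.030 | 0.070 | 81% |

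The gap between the two risk differences is the prevented relapse, 0.05b. It appears only in *worse*. The multinomial ratio of *improved* against *same* moves from 2.02 to 1.86 to 1.73 down the table, although the conditional effects are identical.

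**2. Baseline imbalance with no effect.** Take three categories (0, 1, 2+ times a day), a latent within-child correlation of 0.5 and the same transition probabilities in both arms.

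- Baseline 20/40/40%: P(increased) = 0.245.
- Baseline 17.5/37.5/45%: P(increased) = 0.223; relative risk 0.223 / 0.245 = 0.91.
- Baseline 15/35/50%: P(increased) = 0.200; relative risk 0.200 / 0.245 = 0.82.

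The chance SD of the baseline difference between arms is √[2 × 0.4 × 0.6 / 480 × (1 + 47 × ICC)]. This is 0.044 at ICC 0.02 and 0.058 at ICC 0.05. A 5-point imbalance is about one SD, so it is ordinary.

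**3. Power (simulation).** Assume 10 schools × 48 children per arm, ICC 0.02, within-child correlation 0.5 and a latent shift of 0.25. The shift raises twice-daily brushing from 40% to 50%, 60% to 69% and 30% to 39% in the three rows.

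| Baseline mix (0/1/2+) | *Increased* alone | Joint test, all change categories | Follow-up score, baseline-adjusted | Twice daily, baseline-adjusted |
|---|---|---|---|---|
| 20/40/40 | 55% | 71% | 87% | 81% |
| 10/30/60 | 31% | 64% | 81% | 78% |
| 30/40/30 | 67% | 71% | 88% | 79% |

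The gain over the joint test is 87 − 71 = 16, 81 − 64 = 17 and 88 − 71 = 17 points for the score. For the binary version it is 81 − 71 = 10, 78 − 64 = 14 and 79 − 71 = 8 points. Type I error was 4–6% both for the *increased* contrast and for the adjusted score.

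**The case against.** The strongest reply is that the article never states an increased/same/decreased coding. Transition categories (stayed good, improved, worsened, stayed poor) would also suit a multinomial model and would separate the two stable groups. A reader might infer that the plan definitely scores good-throughout and poor-throughout children alike; the text does not establish that. It is the natural reading of a categorical change, and the point is conditional on it. Likewise, no response options are given, so the bounded ordinal scale is an inference.

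Second, a multinomial model with predictive margins also estimates *decreased*, so prevented relapse would be reported somewhere. This stands. It is why the fair comparator is the joint test, not the *increased* contrast alone. The gap of 21 to 50 points between *increased* alone and the adjusted score (88 − 67 and 81 − 31) overstates the loss under the planned model.

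Third, a reader might infer bias or false positives. The documents and the check do not support that. Type I error holds, and chance imbalance is random error in either direction that a clustered standard error covers. Nor is the effect always understated: with arms balanced at baseline, the simple relative risk of *improved* in the two-level illustration is 0.35 / 0.20 = 1.75 at every baseline mix. The follow-up difference varies with baseline mix too.

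Fourth, the Discussion's remark on behavioural factors shows that baseline adjustment is not excluded, and once the baseline category is conditioned on, the no-effect shift in step 2 disappears. But the remark fixes no covariate, and the adjustment named for the models is socioeconomic.

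Last, change in behaviour is a legitimate question for a behavioural programme. A descriptive transition table answers it without making change the modelled outcome.

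**Conclusion.** The point holds as one of precision and interpretability for two parent-reported secondary outcomes. Sizing and the primary caries analysis are untouched. It is more than missing detail: the article fixes the outcome type (categorical change), the effect measures and the model, and a better analysis of the same data is available.

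Under the stated assumptions, modelling the follow-up category adjusted for baseline gains about 8 to 17 percentage points of power over a joint test of the change categories. It also removes the dependence of the reported result on chance baseline imbalance (relative risk about 0.91 for a 5-point imbalance with no effect). The sizes rest on assumed brushing distributions, an ICC borrowed from the sample-size section, a within-child correlation of 0.5 and direction-of-change coding. At a correlation of 0.3, power for *increased* alone was 43%, 23% and 55%, against 78%, 74% and 81% for the adjusted score, so the direction of the finding does not hinge on 0.5.

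**What to change.** In Between groups comparisons, make the modelled outcome for brushing frequency and for oral-health impact the category reported at follow-up. Use ordinal logistic regression, with a binary (at least twice a day; no impact) or multinomial model if proportional odds fails. Include the child's baseline category and the affluence stratum as covariates and allow for school. Report risk differences and relative risks from predictive margins, as already planned. Show transitions from baseline in a descriptive table. Reword the quality-of-life objective to match: the difference between arms in impact at follow-up, adjusted for baseline.

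The cost is a wording change. No extra data, visits or children are needed, because both answers are already collected at baseline and follow-up. The one downside is that the proportional-odds assumption has to be checked.

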## Discussion

Despite the availability of free dental services in Saudi Arabia, dental caries is still a common disease among children. Many studies have focused on the implementation of school-based programs to promote and tackle the burden of untreated dental caries [34]. This study will take a step further and explore the effectiveness of virtual supervised tooth brushing on untreated dental caries especially since Saudi Arabia has proven to have an effective IT infrastructure for virtual schooling.

Three different outcome measures are used to evaluate the effectiveness of virtual supervised tooth brushing on caries experience. The study’s primary outcome is the change in caries experience—the number of decay (untreated dental caries) missing and filled teeth—in both primary and permanent teeth over 36 months (baseline, + 3 months,+ 6 months + 12 months,+ 24 months, + 36 months from baseline) using the WHO criteria [29]. The secondary outcome will be obtained through both clinical outcomes (plaque and gingival scores) and the self-reported questionnaire to assess the change in the frequency of brushing per day and the impact of oral health on the child’s daily life (QoL) [29]. The selected study design will collect data on participants’ socioeconomic and behavioral factors which will help accounting for baseline differences between the two trial groups.

The findings of this study will provide important information on the impact of virtual supervision on dental caries. A positive impact will be an opportunity for targeting a large portion of the population with a high level of disease as a quarter of the Saudi population is younger than 15 years [1]. A positive finding will also support the continuation of virtual supervised tooth brushing in many schools in other parts of the country. Finally, future research should also investigate the factors that could affect the effectiveness of programs. A national study could provide more details about the effectiveness of the program in many different parts of the country.
